### **9.1.1. Measurability of tumor lesions at baseline**

#### **Definitions**

♦ Measurable lesions - lesions that can be accurately measured in at least one dimension with longest diameter  $\geq 20$  mm. With spiral CT scan, lesion must be  $\geq 10$  mm in at least one dimension.

♦ Non-measurable lesions - all other lesions, including small lesions (longest diameter  $< 20$  mm with conventional techniques or  $< 10$  mm with spiral CT scan) and other non-measurable lesions. These include: bone lesions; leptomeningeal disease; ascites; pleural / pericardial effusion; inflammatory breast disease; lymphangitis cutis / pulmonis; abdominal masses that are not confirmed and followed by imaging techniques; and cystic lesions.

All measurements should be recorded in metric notation by use of a ruler or calipers. All baseline evaluations should be performed as closely as possible to the beginning of treatment and never more than 21 days before the beginning of the treatment.

#### **Tumor response evaluation**

Target lesions should be selected on the basis of their size (those with the longest diameter) and their suitability for accurate repetitive measurements (either by imaging techniques or clinically).

A sum of the longest diameter (LD) for all target lesions will be calculated and reported as the baseline sum LD. The baseline sum LD will be used as reference by which to characterize the objective tumour response.

All other lesions (or sites of disease) should be identified as non-target lesions and should also be recorded at baseline. Measurements are not required but the presence or absence of each should be noted throughout follow-up.

### **9.1.2. Response Criteria**

Patient will be considered in response if they are in complete response (CR), Partial response (PR) or stable disease (SD) as described below.

## Evaluation of target lesions

|                         |                                                                                                                                                                                        |
|-------------------------|----------------------------------------------------------------------------------------------------------------------------------------------------------------------------------------|
| Complete Response (CR): | Disappearance of all target lesions.                                                                                                                                                   |
| Partial Response (PR):  | At least a 30% decrease in the sum of LD of target lesions taking as reference the baseline sum LD.                                                                                    |
| Progression (PD):       | At least a 20% increase in the sum of LD of target lesions taking as references the smallest sum LD recorded since the treatment started or the appearance of one or more new lesions. |
| Stable Disease (SD):    | Neither sufficient shrinkage to qualify for PR nor sufficient increase to qualify for PD taking as references the smallest sum LD since the treatment started.                         |

## Evaluation of non target lesions

|                                      |                                                                                                                   |
|--------------------------------------|-------------------------------------------------------------------------------------------------------------------|
| Complete Response (CR):              | Disappearance of all non-target lesions and normalization of tumor marker level.                                  |
| Incomplete Response / Stable Disease | Persistence of one or more non-target lesion(s) or/and maintenance of tumor marker level above the normal limits. |
| Progression (PD):                    | Appearance of one or more new lesions and/or unequivocal progression of existing non-target lesions (*).          |

(\*) Although a clear progression of “non target” lesions only is exceptional, in such circumstances, the opinion of the treating physician should prevail and the progression status should be confirmed later on by the review panel (or study chair).

## Best overall response

If measurable disease is present at different sites in a given patient, the response is assessed globally for all sites. The best overall response is the best response recorded from the start of the treatment until disease progression/recurrence (taking as reference for progressive disease the smallest measurements recorded since the treatment started). The patient's best response assignment will depend on the achievement of both measurement and confirmation criteria.

| Target lesions | Non-Target lesions       | New Lesions | Overall response |
|----------------|--------------------------|-------------|------------------|
| CR             | CR                       | No          | CR               |
| CR             | Incomplete response / SD | No          | PR               |
| PR             | Non-PD                   | No          | PR               |
| SD             | Non-PD                   | No          | SD               |
| PD             | Any                      | Yes or No   | PD               |
| Any            | PD                       | Yes or No   | PD               |
| Any            | Any                      | Yes         | PD               |

## 9.2. Modified irRC methods

- Overall irCR: Complete disappearance of all lesions (whether measurable or not) and no new lesions. All measurable lymph nodes also must have a reduction in short axis to 10 mm or less.
- Overall irPR: Sum of the longest diameters of target and new measurable lesions decreases  $\geq 30\%$ . (compared to baseline)
- Overall irSD: Sum of the longest diameters of target and new measurable lesions neither irCR, irPR, (compared to baseline) or irPD (compared to nadir).
- Overall irPD: Sum of the longest diameters of target and new measurable lesions increases  $\geq 20\%$  (compared to nadir), confirmed by a repeat, consecutive observations at least 4 weeks (normally it should be done at 6 weeks) from the date first documented

|                               | RECIST 1.1                                                                                                                                                                     | Modified IrRC                                                                                                                                                                       |
|-------------------------------|--------------------------------------------------------------------------------------------------------------------------------------------------------------------------------|-------------------------------------------------------------------------------------------------------------------------------------------------------------------------------------|
| Target /
Index Lesions     | Up to 5 total (2/organ)
unidimensional                                                                                                                                      | Up to 5 total (2/organ), unidimensional                                                                                                                                             |
| New lesions                   | Always represent PD                                                                                                                                                            | Incorporated into SOLD if $\geq 5 \times 5$ mm
(non-nodal) or $\geq 10$ mm (nodal)                                                                                               |
| Non-Target /
Index Lesions | Contribute to define CR, PR, SD and PD                                                                                                                                         | Contribute to define modified IrCR ONLY                                                                                                                                             |
| CR                            | Disappearance of all known lesions;
confirmed at 4 weeks                                                                                                                    | Disappearance of all known lesions;
confirmed $\geq 4$ weeks                                                                                                                     |
| PR                            | At least 30% decrease in SOLD;
confirmed at $\geq 4$ weeks                                                                                                                  | At least 30% decrease in SOLD;
confirmed at $\geq 4$ weeks                                                                                                                       |
| SD                            | Neither PR or PD criteria met                                                                                                                                                  | Neither PR or PD criteria met                                                                                                                                                       |
| PD                            | 20% increase in SOLD compared with
nadir (and absolute increase of 5mm)
and/or unequivocal progressions
of non-target lesions and/or
appearance of
new lesions. | SOLD of target and new measurable
lesions increases $\geq 20\%$
(compared to nadir), confirmed $\geq 4$ weeks
(normally done at 6 weeks) from the date first
documented |

## 9.3. Progression free survival (PFS)

Progression free survival is defined as the time from enrolment until the date of objective disease progression or death (by any cause in the absence of progression). The date of PFS will be recorded by the investigator and defined according to local standard clinical practice and may involve any of: objective radiological progression, symptomatic progression or death. Progression free survival data will be collected at Months 3 and Months 6.

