#### **1.4.1.3 Durvalumab tremelimumab**

The preclinical and clinical justification for this combination as noted in Section 1.1.4 also supports the synergy of this combination. Available data, such as those presented by Wolchok et al, suggest that the combination of agents targeting PD-1/PD-L1 and CTLA-4 may have profound and durable benefits in patients with melanoma (Wolchok et al 2013). Of the 102 subjects with advanced NSCLC treated with durvalumab in combination with tremelimumab in Study D4190C00006, 63 subjects with at least 16 weeks of follow-up were evaluable for response (defined as measurable disease at baseline and at least 1 follow-up scan; this included discontinuations due to disease progression or death without follow-up scan). Of the 63 evaluable subjects, 17 (27%) had a best overall response of PR, 14 (22%) had SD, 22 (35%) had PD, and 10 (16%) were not evaluable. The ORR (confirmed and unconfirmed CR or PR) was 27% and the DCR (CR, PR, or SD) was 49% as assessed by RECIST v1.1.

Current experience with single-agent IMT studies suggests that clinical responses may be restricted to a subset of any given patient population and that it might be beneficial to enrich the patient population by selecting patients likely to respond to therapy. To date, no assay has been established or validated, and no single approach has proven accurate, for patient enrichment for IMTs. However, independent data from multiple sources using different assays and scoring methods suggests that PD-L1 expression on tumor cells and/or tumor infiltrating cells may be associated with greater clinical benefit.

Data from ongoing studies with durvalumab and other agents targeting the PD-1/PD-L1 pathway suggest, as shown in a number of tumor types (eg, NSCLC, renal cell carcinoma, and melanoma), that monotherapy may be more efficacious (in terms of ORR) in patients who are PD-L1-positive.

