## **9. DISEASE EVALUATION AND METHODS**

The response to immunotherapy may differ from the typical responses observed with cytotoxic chemotherapy including the following (Wolchok et al 2009, Nishino et al 2013):

- Response to immunotherapy may be delayed
- Response to immunotherapy may occur after PD by conventional criteria
- The appearance of new lesions may not represent PD with immunotherapy
- SD while on immunotherapy may be durable and represent clinical benefit.

Based on the above-described unique response to immunotherapy and based on guidelines from regulatory agencies, e.g., European Medicines Agency's "Guideline on the evaluation of anti-cancer medicinal products in man" (EMA/CHMP/205/95/Rev.4) for immune modulating anti-cancer compounds, the study may wish to implement the following in addition to standard RECIST 1.1 criteria:

- RECIST will be modified so that PD must be confirmed at the next scheduled visit, preferably, and no earlier than 4 weeks after the initial assessment of PD in the absence of clinically significant deterioration. Treatment with durvalumab + tremelimumab would continue between the initial assessment of progression and confirmation for progression.
- In addition, subjects may continue to receive durvalumab + tremelimumab beyond confirmed PD in the absence of clinically significant deterioration and if investigators consider that subjects continue to receive benefit from treatment.

Modification of RECIST as described may discourage the early discontinuation of durvalumab + tremelimumab and provide a more complete evaluation of its anti-tumor activity than would be seen with conventional response criteria. Nonetheless, the efficacy analysis will be conducted by programmatically deriving each efficacy endpoint based on RECIST 1.1 criteria.

Of note, clinically significant deterioration is considered to be a rapid tumor progression that necessitates treatment with anti-cancer therapy other than durvalumab + tremelimumab or with symptomatic progression that requires urgent medical intervention (e.g., central nervous system metastasis, respiratory failure due to tumor compression, spinal cord compression).>>

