### **11.3.2. Efficacy Analyses set**

Efficacy analyses will be performed in modified intent-to-treat population (ITT) population ie, all patients following the major inclusion criteria and with a 3 months evaluation. Analyses will be repeated in the intent to treat principle i.e including all enrolled patients whatever eligibility criteria and treatment received patients and in the per protocol population (patients who had received all the planned doses).

The primary objective will be evaluated at 3 months among MSS patients only. According to the Simon's design, at 3 months, on the first evaluable 43 patients (mITT population): if 26 or more patients respond to treatment the treatment will be considered of interest for evaluation in a phase III trial. Response rates will be evaluated using RECIST criteria. Response will be considered for patient with Complet response (CR), partial response (PR) and stable disease (SD). Overall survival and progression free survival (OS and PFS) will be estimated using Kaplan Meier method. Median survivals will be reported with 95% confidence intervals (CI).

Median follow-up will be estimated using the reverse Kaplan Meier method.

Analysis of survival and response among MSI patients will be performed in an exploratory manner, taken into account the small sample size in this population. All statistical analysis will be performed with Stata 11 or SAS 9.3.

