#### **11.4. Determination of sample size**

**Step 1:** Nine patients will be included in the **safety** analyses. If the same grade 3-4 adverse event is reported for more than 1 patient over 3, the trial could prematurely stop after reunion of the independent committee. Patients from the safety population will be included in the efficacy set.

**Step 2:** The **efficacy** will be determined using a Simon 2 steps phase II design.

The hypotheses are the following:

The primary objective will be evaluated among MSS patients

A PFS of 3 months is not considered of interest. A PFS of 6 months is expected. This is equivalent to assume that a PFS of 50% at 3 months is insufficient and a PFS of 70.7% is expected. With  $\alpha=10\%$ ,  $\beta=10\%$  (90% power), 20% of non-evaluable patients, 52 patients with MSS disease are needed including patients of the safety population (9 patients)

The prevalence of MSS disease is around 90%-95%, thus 5 additional patients will be included

Overall the study will include 57 patients.

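### Progression and response are each defined in conflicting ways, so PFS, the 3-month count and the secondary response rate need one definition apiece

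*Protocol*

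**What the plan says.** **Progression.** The synopsis (Step 2 efficacy assessments) lists PFS under RECIST 1.1, and section 9 says "the efficacy analysis will be conducted by programmatically deriving each efficacy endpoint based on RECIST 1.1 criteria". Section 9.3 starts from objective progression or death, but then has the investigator record a date that is "defined according to local standard clinical practice and may involve any of: objective radiological progression, symptomatic progression or death".

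**Target-lesion progression.** Section 9.1.2, under the RECIST 1.1 heading, asks for "At least a 20% increase in the sum of LD of target lesions", measured from the smallest sum since treatment started, with no absolute minimum. The RECIST 1.1 column of the table in section 9.2 asks for a 20% increase from "nadir (and absolute increase of 5mm").

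**Decision count.** Section 11.3.2 calls the treatment of interest if at least 26 of the first 43 evaluable MSS patients respond at 3 months by RECIST: "Response will be considered for patient with Complet response (CR), partial response (PR) and stable disease (SD"). The hypotheses in section 11.4 are progression-free rates: "This is equivalent to assume that a PFS of 50% at 3 months is insufficient and a PFS of 70.7% is expected".

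**Response.** Section 9.1.2 also counts stable disease as response. Footnote i of the schedule of assessments gives RECIST response as CR or PR with a confirmatory scan. Response to treatment is a secondary objective (section 2.2) and has no definition of its own.

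**Collection.** Section 9.3 adds: "Progression free survival data will be collected at Months 3 and Months 6". Section 9.1 requires tumour assessments until documented progression, and Figure 1b schedules CT into month 24.

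**The concern.** PFS is the stated phase II primary objective, and the hypotheses are PFS rates. The efficacy decision, however, is a count of RECIST categories. If section 9.3 defines PFS, the Kaplan-Meier curve and the count can classify the same patient differently. In an open-label, single-arm trial at nine sites, an event rule tied to local practice may also differ between sites. The 5 mm discrepancy is separate. Both versions carry the RECIST 1.1 label, so section 9's reliance on RECIST 1.1 does not settle which applies. A secondary response rate that includes stable disease would be a disease control rate, yet could be read as tumour shrinkage.

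**Working it through.** **1. The plan's own figures.** Inputs are p0 = 0.50 and p1 = 0.707 (section 11.4), continue if at least 9 of 16 (section 11.3.4), and success if at least 26 of 43 (section 11.3.2). Under exponential PFS, a 3-month median gives 0.5^(3/3) = 0.50 at 3 months, and a 6-month median gives 0.5^(3/6) = 0.707. The exact probability of a positive trial is

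P(p) = Σ over x = 9 to 16 of C(16,x) p^x (1−p)^(16−x) × P[Bin(27,p) ≥ 26 − x].

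P(0.50) = 0.0931 and P(0.707) = 0.9014. An exhaustive search returns 8/16, 25/43 as the Simon optimal design for these inputs. The design arithmetic holds.

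**2. Patients the text classifies in two ways.**

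| Patient at 3 months | One reading | Other reading |
|---|---|---|
| Symptomatic progression, RECIST SD | Event (9.3) | Success (11.3.2) |
| Target sum up by at least 20% but under 5 mm, no other sign of progression | PD, failure (9.1.2) | SD, success (RECIST 1.1 column, 9.2) |
| Stable disease, for the secondary response rate | Responder (9.1.2, 11.3.2) | Not a responder (footnote i) |

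**3. Reach of the 5 mm conflict.** A rise of at least 20% can be under 5 mm only if 0.20 × S < 5, that is, if the reference sum S is below 25 mm. The first on-treatment CT is at visit 6, so at the 3-month decision the reference is the baseline sum. The conflict affects only patients with a baseline target sum below 25 mm whose sum grows by at least 20%.

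**4. Sensitivity of the 26-of-43 rule.** The documents give no rate of disagreement between definitions, so these shifts are assumptions. One patient in 43 is 2.33 percentage points.

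| Assumed true success rate | Change | Probability of a positive trial |
|---|---|---|
| 0.707 | none | 0.901 (power) |
| 0.684 | 1 patient fewer | 0.84 |
| 0.660 | 2 patients fewer | 0.76 |
| 0.607 | 10 points lower (43 × 0.10 = 4.3 patients) | 0.51 |
| 0.50 | none | 0.093 (type I error) |
| 0.52 | 2 points higher | 0.14 |
| 0.55 | 5 points higher | 0.25 |

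At the boundary, one reclassified patient (26 to 25) reverses the conclusion.

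**5. Who is in the 43.** Section 11.3.2 limits the modified ITT set to patients with a 3-month evaluation. Someone who dies or deteriorates clinically before the scan may drop out of the denominator instead of counting as a failure, which would push the observed rate upwards. A clearer progression definition alone does not cure that.

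**The case against.** The strongest reply is that the decision rule is written only once, in RECIST categories, and that the synopsis and section 9 both point to RECIST 1.1. On that reading section 9.3 governs only the recorded PFS date and the Kaplan-Meier curve. This largely stands. The count is not undefined, and the table in step 4 does not predict an error. The reply does not remove the disagreement between the named primary endpoint and the count, nor the two RECIST-labelled progression rules.

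Four stronger readings are tempting, and the documents do not support them.

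- *That including stable disease spoils the primary count.* CR+PR+SD at 3 months approximates being progression-free at 3 months, which is what the 50% and 70.7% describe. The stable-disease problem concerns the secondary response rate.
- *That PFS data stop at month 6, so the median may not be reached.* Section 9.1 and the CT schedule contradict this. The sentence needs aligning, no more.
- *That the gap in section 1.4.1.3 measures the effect here:* "The ORR (confirmed and unconfirmed CR or PR) was 27% and the DCR (CR, PR, or SD) was 49"%. Those patients had NSCLC and received the two antibodies. The figures show only that the protocol elsewhere calls CR+PR+SD disease control.
- *That section 9's confirmation of progression is a further competing definition.* Section 9 itself returns the efficacy analysis to RECIST 1.1.

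**Conclusion.** The point holds as a set of internal contradictions. Progression is RECIST-derived in the synopsis and section 9 but set by local practice in section 9.3. The RECIST 1.1 target-lesion rule has two versions, which differ only when the reference sum is below 25 mm. Response has two meanings, so the secondary objective can be read as a disease control rate. No stated number is wrong on this point.

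The size is conditional. Under the assumed shifts, power runs from 0.84 (one patient) to 0.51 (10 points), and type I error is 0.14 or 0.25 at a null rate of 52% or 55%. The documents do not say how often the definitions would disagree. The change should be made because it is cheap and bears on the trial's only efficacy decision.

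**What to change.** 1. Use one progression definition for both PFS and the 3-month count: RECIST 1.1 progression (a 20% and 5 mm increase, a new lesion, or unequivocal non-target progression) or death. Remove the local-practice sentence from section 9.3.
2. Align section 9.1.2 with the RECIST 1.1 column in section 9.2.
3. State that patients who die or progress clinically before the 3-month scan stay in the 43 as failures. Amend the 3-month evaluation condition in the modified ITT definition (synopsis, sections 11.2.2 and 11.3.2) to match, and check the replacement rule in section 6.1.3 against it. Say how clinical progression without imaging enters the PFS analysis, so that curve and count agree.
4. Rename the 26-of-43 count the 3-month progression-free rate. Define secondary response as CR+PR, consistent with footnote i, and report disease control separately.
5. Align the months 3 and 6 sentence with section 9.1, as a consistency edit.

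The scans are already scheduled, and the Simon boundaries and sample size stay as they are. Items 1, 2, 4 and 5 are wording. Item 3 changes who is analysed, so it should be settled before the count is made.
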